#### Sensitivity analyses

*Death as a competing risk*: should incidence of death be substantial as a competing risk event, a multivariable Fine & Grey regression model^28^ adjusted for the minimisation factors may be fitted to the primary outcome measure.*Treatment adherence*: patterns of treatment adherence will be explored, and an appropriate statistical method taking adherence into account while respecting the randomisation (eg, rank preserving structural or structural nested failure time model^29–31^ or marginal structural model)^32
33^ will be used to model causal treatment effect for observed adherence.*Alignment with Health Economic analysis*: a parametric model consistent with that which is required in the health economic analyses (see Economic Evaluation section) for providing transition probabilities beyond the time frame of the trial will be fitted to the primary outcome measure.

#### Analysis of secondary outcome measures

*Wound infection measured by modified Bluebelle (WHQ*): a multivariable, random coefficients, repeated measures linear regression model will be fitted to modified Bluebelle WHQ score over time (until complete wound healing), including minimisation factors and randomised treatment. Centre, participant and participant-by-time interaction random effects will be explored. Time, treatment and treatment-by-time interaction will be fitted as fixed effects. An estimate for the magnitude of the treatment-by-time interaction and corresponding 2-sided 95% CI will be reported.*Number of days prescribed antibiotics for infection of the wound*: a multivariable Poisson regression model will be fitted to whether participant has been prescribed antibiotics over time, with an offset term for time at risk of being on antibiotics, including the minimisation factors and randomised treatment. Centre and participant random effects will be explored. An estimate for the difference in number of days where antibiotic prescribed and 95% CI will be reported.*Scar Quality (POSAS*): a multivariable linear regression model will be fitted to both participant and clinician POSAS scores, including the minimisation factors and randomised treatment. Centre random effects will be explored. Estimates for the differences in POSAS scores between the SC and SC+CT arms and 95% CIs will be reported.*Safety*: events including related complications and hospitalisations to healing (maximum 52 weeks post randomisation) will be summarised descriptively by treatment received.*Associations between partial closure method, post partial closure wound area and time to healing*: partial wound closure method and post-partial closure wound area will be included as additional covariates in the primary endpoint analysis model as described above. Wound area at baseline and 4 weeks post randomisation will be calculated using the elliptical method^34^ from maximum length and width measurements provided by site; time to complete wound healing will be determined as per the primary endpoint measure.

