#### Secondary objectives

To compare groups for:

Incidence of infection as measured by modified Bluebelle Wound Healing Questionnaire (WHQ)^20^ until healing.Numbers of days participants prescribed antibiotics until healing.Scar quality as measured by Patient and Observer Scar Assessment Scale (POSAS).^21^Safety events including related complications and hospitalisations until healing (maximum 52 weeks post randomisation).Cost-effectiveness via a within-trial analysis and decision analytic model (DAM) assessed from a payer perspective measuring patient health-related quality of life in terms of Quality Adjusted Life Years (QALYs) meeting updated Consolidated Health Economic Evaluation Reporting Standards (CHEERS) 2022 updated reporting guidance.^22^Resource use and health-related quality of life (HRQoL) as measured by EuroQol 5 Dimensions 5 Levels questionnaire (EQ-5D-5L) to 26 weeks post randomisation (52 weeks where applicable, for unhealed participants only).The relationship between post-partial closure wound area, type of partial closure method, and time to healing.

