#### Baseline assessment on the day of surgery/randomisation

Demographic information.Relevant medical history and clinical assessments.ABPI or Toe Pressure.CEAP.Factors affecting healing.Mobility.Questionnaire.EQ-5D-5L.In theatre.Post excision wound measurement – length, width, depth (excision to fat/excision to fascia or periosteum).Type of partial closure (purse string suture, side-to-side partial closure, eg, with pulley sutures or buried sutures, none).Post partial closure measurement (where applicable) – length and width.Following randomisationParticipant trial ID number.Randomisation allocation and details of intervention application.Date.Antibiotics.Related expected adverse and SAEs.

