#### Week 12 postal/electronic data collection

Questionnaires.Modified Bluebelle WHQ (if unhealed).EQ-5D-5L.Health Resource Use.

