#### Modified bluebelle wound healing questionnaire (WHQ)

The modified Bluebelle WHQ^20^ has been adapted from the original Bluebelle WHQ^25^ for relevance for patients with open wounds by removing three items relating to spontaneous or deliberate wound dehiscence and use of dressings given these would not be relevant in this population. The time frame for the questionnaire has also been adapted to indicate that the questionnaire should be completed since the participant had their open wound (at wound healing or since the last modified Bluebelle questionnaire was completed – weeks 4, 12, 26 and 52 weeks (where applicable, if wound is not healed)) post randomisation and at healing, where applicable rather than the time since hospital discharge.

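### The infection objective is about incidence, but the only effect named for it is a treatment-by-time interaction on the WHQ score, which can miss a real benefit

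*Protocol article*

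**What the plan says.** In the Protocol article, Secondary objectives, the first item for comparison between groups is "Incidence of infection as measured by modified Bluebelle Wound Healing Questionnaire (WHQ"), until healing.

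Under Analysis of secondary outcome measures, the wound infection entry specifies a random-coefficients, repeated-measures linear model of the WHQ score up to complete healing, with the minimisation factors. On the treatment terms it says: "Time, treatment and treatment-by-time interaction will be fitted as fixed effects". The only estimate then named is this one: "An estimate for the magnitude of the treatment-by-time interaction and corresponding 2-sided 95% CI will be reported".

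On timing:
- The baseline assessment lists one questionnaire, the EQ-5D-5L, so there is no baseline WHQ.
- The week 4 visit lists the WHQ without restriction.
- The week 12 list reads "Modified Bluebelle WHQ (if unhealed"), and week 26 has the same limit. The week 52 questionnaires are for wounds still unhealed.
- The WHQ section adds a completion at healing and sets the recall period as "at wound healing or since the last modified Bluebelle questionnaire was completed".

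The article gives no score threshold, event definition, proportion, rate or odds ratio for infection.

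**The concern.** An incidence answers how many participants in each arm had an infection. A treatment-by-time interaction answers whether the arms' mean scores drift apart or together over follow-up. The two can disagree, and an arm with far fewer infections can show no interaction at all.

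The design makes this relevant. Compression starts on the day of surgery and part of its rationale is postoperative oedema, so an early effect is plausible. The first scheduled score is at week 4, so an effect in weeks 0 to 4 is already present in that score. It falls mainly in the treatment main effect, which is fitted but not named for reporting.

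Infection affected 30.2% (16 of 53) of the feasibility cohort, and the patient group named it as an important outcome. The risk is that a real difference in infection is reported as none.

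**Working it through.** **1. The plan's own figures.** No figure is stated for the infection analysis. The planning effect used below reproduces: 0.70 × 81 = 56.7, given as 57 days; 1/0.70 = 1.43, the stated HR.

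**2. What the interaction measures.** Write the mean score as a + b·t + c·trt + d·trt·t, with t in weeks. The reported quantity is d.
- Benefit of δ points at every visit from week 4: c = −δ and d = 0.
- Benefit of δ at week 4 that has gone by week 12: the arm difference moves from −δ to 0 over 8 weeks, so d = +δ/8 per week. A positive sign reads as harm.

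Neither result needs an assumed infection rate.

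**3. Who supplies the later scores.** With exponential healing, the unhealed share at day x is 2^(−x/median).

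| Week | SC (median 81 days) | SC+CT (median 57 days) |
|---|---|---|
| 4 | 2^(−28/81) = 79% | 2^(−28/57) = 71% |
| 12 | 2^(−84/81) = 49% | 2^(−84/57) = 36% |
| 26 | 2^(−182/81) = 21% | 2^(−182/57) = 11% |
| 52 | 2^(−364/81) = 4% | 2^(−364/57) = 1% |

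The week 12 row depends little on the exponential shape. Day 84 is 3 days past the SC median, and under proportional hazards the SC+CT share is 0.487^1.43 = 0.36. The week 26 row is probably too high. The feasibility cohort had 7.5% unhealed and 7.5% of unknown status at 6 months, so SC may lie between 7.5% and 15% (8/53). SC+CT would then lie between 0.075^1.43 = 2% and 0.151^1.43 = 7%. On either basis the later scheduled scores come from small subsets whose make-up depends on the primary treatment effect.

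**4. Recall windows.** Scheduled completions cover 4, 12 − 4 = 8, 26 − 12 = 14 and 52 − 26 = 26 weeks, or a shorter period ending at healing. One infection therefore counts in windows of very different length.

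**5. How often it would matter (illustration only).** The documents give neither the timing of infections nor the score change they cause. These inputs were assumed:
- 178 per arm (198 × 0.90) and healing medians of 81 and 57 days;
- infection rate 0.06 per week to week 4, 0.015 to week 12 and 0.01 after;
- a personal factor that slows healing and raises infection;
- a 6-point score rise in the window containing the infection;
- a random-intercept model without random slope or minimisation factors, and 150 simulated trials.

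With the infection rate halved throughout (incidence 32% v 17%), the interaction was significantly in favour of CT in 0% of trials, had the wrong sign in 81%, and was significantly against CT in 12%. With benefit in weeks 0 to 4 only (33% v 17%), those figures were 0%, 96% and 48%.

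Under other assumptions (8-point rise, 60 trials) and halving throughout, the wrong sign occurred in 42–43% of trials with a constant infection rate and 75–82% with an early-weighted one. In those runs significance in favour was 0–5%, and significance against never exceeded 17% in any scenario. Missing the benefit was stable across these assumptions. The sign was not.

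**The case against.** The article points to a SAP and a full protocol, and it does not say the interaction is the only quantity that will be reported. The treatment main effect is already in the model. A linear time trend is inferred from the random-coefficients wording and is not spelled out. Infection is also approached elsewhere: days on antibiotics for wound infection are compared between arms, related infections are captured by record review, and related complications and hospitalisations are summarised.

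Much of this limits the weight of the point but does not remove it. The unseen documents may add contrasts, yet this article states an incidence objective and names a different quantity as its result. Antibiotic days measure prescribing. The safety summaries are descriptive and by treatment received, so they are not a randomised comparison of incidence.

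A reader might infer that the analysis would reverse a real benefit. The documents do not support that as a general statement. A wrong sign needs the benefit to be concentrated early, and the percentages above rest on assumed infection rates and score changes in a simplified model. A reader might also infer that unequal recall windows make any time trend meaningless. They make it harder to interpret, but that alone does not invalidate it.

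**Conclusion.** The objective and the reported effect do not match as written, and the plan should be corrected. The interaction is not an incidence, equals zero under a constant score benefit from week 4, and leaves an effect in weeks 0 to 4 mainly in a term not named for reporting. These conclusions follow from the text and the model's algebra. The later scores compare groups selected by treatment, about 49% v 36% unhealed at week 12. That figure assumes the planning effect holds, with exponential healing or proportional hazards at HR 1.43.

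The possible shift towards apparent harm is real in direction for an early benefit that fades, but its size and frequency cannot be established from the documents. The outcome is secondary. The primary endpoint, sample size, randomisation and data collection are untouched, so this is a should-fix point.

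**What to change.** In Analysis of secondary outcome measures, make the reported infection effect a between-arm comparison of the proportion with wound infection from randomisation to healing or to a fixed time. Analyse it by randomised group, adjusted for the minimisation factors, with death and withdrawal handled explicitly. Fix the infection event before unblinding, either as a WHQ-based rule or from infection data already collected.

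For the WHQ score, report the adjusted treatment difference at week 4, using the at-healing score for those healed earlier. This also settles an ambiguity: the week 4 visit list has no healing restriction, but the WHQ section's wording ("since the last modified Bluebelle questionnaire was completed – weeks 4, 12, 26 and 52 weeks (where applicable, if wound is not healed") could be read as applying one. Keep the treatment-by-time interaction as supportive only.

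If no valid infection event can be defined, reword the objective to WHQ score and report that treatment difference.

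The cost is wording in the protocol and SAP; no new data are needed. The article gives no cut-off for the modified scale, from which three items were removed, so a definition must be justified and will carry some misclassification. Power for incidence is also limited. With 178 per arm and 30.2% in SC, a two-proportion test has about 93% power against 15%, 60% against 20% and 19% against 25%. The SC+CT rates are assumptions, and error-free classification is assumed.

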#### Exploratory analyses

*Development of a predictive marker of healing*: a multivariable model to predict time to complete wound healing incorporating the minimisation factors and Week 4 measurements of reduction in wound area from baseline will be developed in line with the Prognosis Research Strategy (PROGRESS) initiative.^35–38^*Intervention acceptability and treatment adherence*: both will be summarised descriptively overall, and treatment adherence will also be summarised by randomised treatment group.*Post wound healing breakdown*: descriptive summaries including proportions of index wound status 1 month post healing confirmation (wound healing maintained or wound breakdown) by randomised treatment group and overall will be presented.

#### Missing data considerations

The extent of missing data for each primary and secondary endpoint will be presented by trial arm along with reasons where available. Missing data strategies appropriate for each primary and secondary analysis will be employed. For example, should primary endpoint censoring appear informative, inverse probability of censoring weighting may be used. Further details on how missing data will be handled in each analysis are included in the SAP.

### Economic evaluation

The economic evaluation will assess the cost-utility of SC+CT compared to SC alone using within-trial analysis and a DAM to assess the argument over a longer time perspective. The proposed methods for the economic evaluation will follow the reference case set out by NICE.^39^

The within-trial analysis will be undertaken to estimate the resource use, costs and effects for both comparator arms for the 26-week follow-up period. The DAM will be developed over the course of the project, extrapolating to 52 weeks to help in assessing alignment with and validation by the within-trial analysis and providing some insight on cost-effectiveness drivers. The DAM will be based on a Markov model with states based on healed, unhealed, infected and dead. An NHS and Personal Social Services perspective for costs will be adopted.

Health resource use data will be collected from a questionnaire (see Data Collection and Questionnaire section) and from trial case report forms (CRFs). The information will include primary, secondary and community resource use. Unit cost data will be obtained from national databases such as the *National Schedule of Costs* (NHS England), the *Personal Social Services Research Unit (PSSRU) Costs of Health and Social Care* and the *British National Formulary (BNF*). All resource use will be valued in monetary terms using appropriate UK unit costs with the price year for which all costs can be valued and required adjustments made for inflation using the Office of National Statistics (ONS) Gross Domestic Product (GDP) deflator index.

Treatment costs include the costs of CT and of SC post-op care and wound management (clinic visits, dressings provided, staff time). Participants’ responses to the EQ-5D-5L questionnaire will be converted to utility scores using the newly published UK value set for the 5L version.^40^

Results of the primary economic analysis will be presented as incremental cost-effectiveness ratios (ICERs) for each arm expressed in terms of QALYs. Incremental net monetary benefit and incremental net health benefit statistics will also be computed. NICE considers a cost per QALY within the range of £20 000–£30 000 to be acceptable. The approach to missing data will follow good practice guidelines for cost-effectiveness analysis alongside clinical trials.^41^ Analytical techniques will be jointly determined with the statistical co-applicants to ensure consistency across the project (eg, multiple imputation techniques). Deterministic and probabilistic sensitivity analyses will be used to assess the impact of uncertainty on the results. A health economic analysis plan containing details of the economic evaluation to be conducted will be prepared before the completion of data collection.

### Qualitative sub-study

The qualitative research sub-study will be in the form of virtual semi-structured interviews. These will be audio recorded, transcribed and analysed.

#### Data collection

Up to 25 patients will be identified to achieve a demographic spread and to achieve data adequacy, that is, adequate depth and variety of data to sufficiently answer the study questions. We aim to have representation from most of our recruiting centres with a spread of demographics. We will use a purposeful sampling framework to include those who have found the CT to be acceptable and unacceptable, using specific characteristics (see table 1 below).

**Table 1 T1:** Purposeful sampling characteristics guide

Purposeful sampling factors		Minimum number of patients
	Functional status	
Patients	Self-caring (applies CT themselves) Needs care (needs assistance with CT)	3 3
	Age	
	<65 years ≥65 years	4 4
	Sex	
	Male Female	5 5
	Prior experience with CT	
	Yes No	3 3
	Type of CT	
	Bandaging Compression hosiery	3 3
	Duration of CT	
	Undergoing CT <6 weeks Undergoing CT >6 weeks	2 2
	Completion of CT	
	Full completion Ongoing active therapy Discontinued	2 2 2
	Experience with CT	
Hospitals	Routinely provides CT prior to trial Does not routinely provide CT prior to trial	3 3

The interviews will be guided by a topic guide covering various aspects related to CT, including effectiveness, comfort, challenges, impact on daily activities, pain levels, duration of treatment, satisfaction with healthcare support and factors influencing treatment continuation. The topic guide is developed based on our previous research and informed by the responses to the Intervention Acceptability Questionnaire administered 4 weeks after CT allocation and discussions with members of the trial team, with PPI.

Interviews will be recorded and transcribed verbatim using a University of Leeds approved transcription service. Data will be subject to thematic analysis of the qualitative data obtained from the interviews, guided by The Framework Method.^42^ An iterative-inductive approach will be employed to generate emergent categories and ideas based on specific observations on patient experiences rather than prior concepts, ensuring diversity and complexity in the analysis. Additionally, we aim to respect individual cases while identifying comparative themes and patterns. The transcripts will be coded into themes and sub-themes to identify patterns, common experiences and key findings. Iterative analysis will allow for the emergence of new themes while refining the coding framework.

### Data management

All information collected during the trial will be kept strictly confidential. Information will be held securely on paper and electronically at the Leeds CTRU. The CTRU will comply with all aspects of the 2018 Data Protection Act and operationally this will include:

Consent from participants to record personal details including name*, date of birth*, address and telephone number, email address, NHS or CHI number, hospital number, GP name and address.Appropriate storage, restricted access and disposal arrangements for participant personal and clinical details.Consent from participants for access to their medical records by responsible individuals from the research staff or from regulatory authorities, where it is relevant to trial participation.Consent from participants for the data collected for the trial to be used to evaluate safety and develop new research.Participant name, address, email address and telephone number will be collected when a participant is randomised into the trial but all other data collection forms that are transferred to or from the CTRU will be coded with a trial number and will include two participant identifiers, usually the participant’s initials and date of birth.Where central monitoring of source documents by CTRU (or copies of source documents) is required (such as scans or local blood results), the participant’s name must be obliterated by site before sending.Where anonymisation of documentation is required, sites are responsible for ensuring only the instructed identifiers are present before sending to CTRU.

If a participant withdraws consent from further trial treatment and/or further collection of data their data will remain on file and will be included in the final study analysis.

### Data monitoring

Data will be routinely monitored for quality and completeness by the CTRU. Missing data items are automatically flagged. Targeted strategies for identifying compliance issues and obtaining these data items will be undertaken, including monitoring data return progress, escalation where required and proactively offering assistance and support to research teams at sites. Data will be chased until it is received, confirmed as not available or the trial is at analysis. However missing data items will not be chased from participants (although missing questionnaires sometimes are). The (CTRU/Sponsor) will reserve the right to intermittently conduct source data verification exercises on a sample of participants, which will be carried out by staff from the (CTRU/Sponsor). Source data verification will involve direct access to patient notes at the participating hospital sites and the ongoing central collection of copies of consent forms and other relevant investigation reports.

